#### Patient-Completed Measures

Participants will complete electronic questionnaires at baseline (visit 1b), 4-week follow-up (visit 2), and 8-week follow-up (visit 3), as detailed in Table 1. These include measures of daytime sleepiness using the Epworth Sleepiness Scale (ESS) [27], sleep-related quality of life using the Functional Outcomes of Sleep Questionnaire (FOSQ-10) [28], and patient satisfaction using the Patient Satisfaction Questionnaire (PSQ-18) [29]. Participants will report oral appliance–related side effects, including jaw pain, tooth discomfort, and bite changes, at each follow-up visit. They will also undergo a bruxism screening assessment at baseline (visit 1b) using the BruxScreen-Q [30]. Participant demographic characteristics and baseline information will be collected at visit 1b.

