**Methods:**

This prospective, multisite, observational feasibility study will enroll approximately 60 adult patients with physician-diagnosed obstructive sleep apnea receiving OAT from 10 dental practitioners within the South Texas Oral Health Network, with each practitioner enrolling up to 6 patients. Practitioners will apply either standard signs-and-symptoms–based titration or enhanced multimethod positioning titration, as per their usual clinical practice. Clinical, dental, and titration characteristics will be collected at baseline and follow-up visits over an approximately 8-week titration period. The primary outcome is mean disease alleviation, calculated as the product of physiologic efficacy (change in apnea–hypopnea index derived from multinight home sleep apnea testing) and objective adherence (hours of nightly oral appliance use captured via an embedded compliance tracker). Secondary outcomes include daytime sleepiness, sleep-related quality of life, patient satisfaction, oral appliance–related side effects, and bruxism. Descriptive analyses and generalized estimating equation models will be used to account for clustering of patients within practitioners.

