### Data Collection Procedures and Variables

#### Overview

All study data will be collected electronically using a secure REDCap accessible via tablets, smartphones, or computers. Dentist-reported clinical data, patient-reported outcomes, and device-generated measures will be captured using standardized electronic case report forms and integrated data systems. A comprehensive summary of all variables, measurement instruments, variable roles, and data collection time points is provided in Table 1.

**Table 1. T1:** Study variables, measures, and data collection schedule for dentists and patients.

Measurement category	Variable	Variable role^a^	Instrument and source	Time points
Dentists				
Dentist characteristics	Age, sex, years in practice, DSM^b^ training, practice type, referral patterns	Predictor	Dentist demographics form	Baseline
Eligibility	Inclusion and exclusion confirmation	Screening variable	Inclusion and exclusion criteria form	Visit^c^ 1 a
OSA^d^ risk screening	STOP-BANG score	Predictor	STOP-BANG questionnaire	Visit 1 a
Bruxism assessment	Bruxism screening (clinical indicators)	Predictor and clinical assessment	BruxScreen-C questionnaire and dental exam	Visit 1 a
Dental & airway characteristics	Occlusion, range of motion, TMJ^e^ tenderness, airway anatomy	Predictor	Dental examination form	Visit 1 a
Device selection	Appliance type, design features, rationale	Predictor	Device selection form	Visit 1b
OAT^f^ Titration Strategy	Standard versus enhanced titration	Primary Predictor (Exposure)	Device titration form	Visit 1b; Visit 2; Visit 3
Titration characteristics	Mandibular position, advancement increments, and number of adjustments	Predictor	Device titration form	Visit 1b; Visit 2; Visit 3
Clinical symptom monitoring	Snoring, fatigue, and witnessed apneas	Predictor and clinical monitoring	Dentist documentation	Visit 1b; Visit 2; Visit 3
Clinician-observed side effects	Dental discomfort, occlusal changes	Outcome (secondary)	Dentist report	Visit 2; Visit 3
Study participation	Visit completion, withdrawals, protocol deviations	Feasibility Outcome	Study tracking logs	Throughout study
Patients				
Participant characteristics	Age, sex, race and ethnicity, education, income, insurance	Predictor	Patient demographics questionnaire	Visit 1b
Bruxism assessment	Bruxism symptoms and behaviors	Secondary outcome	BruxScreen-Q questionnaire	Visit 1b
Daytime sleepiness	ESS^g^ score	Secondary outcome	Epworth Sleepiness Scale	Visit 1b; Visit 2; Visit 3

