Sleep-related quality of life	FOSQ-10^h^ score	Secondary outcome	FOSQ-10 questionnaire	Visit 1b; Visit 2; Visit 3
Patient satisfaction	Satisfaction with dental sleep care	Secondary outcome	PSQ-18^i^	Visit 3
Patient-reported side effects	Jaw pain, tooth discomfort, bite changes	Secondary outcome	Sleep and Side effects questionnaire	Visit 1b; Visit 2; Visit 3
Physiologic sleep measures	AHI^j^, RDI^k^, SpO2 nadir, time <90% oxygen saturation	Primary outcome Component	NightOwlHSAT^l^	Visit 1b; Visit 2; Visit 3
Objective adherence	Hours of nightly oral appliance use; head position	Primary outcome component	DentiTrac compliance tracker	Continuous; summarized at Visit 2 and Visit 3
Treatment effectiveness	MDA^m^	Primary outcome	Derived (AHI × adherence)	Visit 2; Visit 3
Patient experience	Perceived benefit, willingness to continue therapy	Exploratory outcome	Patient questionnaire	Visit 3

a Variable roles: predictor variables represent dentist, patient, or clinical characteristics that may influence treatment outcomes. Outcome variables include patient-reported outcomes, clinician-observed effects, feasibility indicators, and the primary effectiveness outcome. Physiologic sleep measures and objective adherence data are combined to derive the primary outcome MDA, calculated as treatment efficacy (change in AHI measured by NightOwl HSAT) multiplied by objective adherence (hours of nightly oral appliance use recorded by the DentiTrac compliance micro tracker).

b DSM: dental sleep medicine.

c Visit definitions: Visit 1a = eligibility screening, consent, and baseline dental examination/clinical assessment; Visit 1b = oral appliance delivery and baseline questionnaires; Visit 2 and Visit 3 = follow-up visits during the titration period.

d OSA: obstructive sleep apnea.

e TMJ: temporomandibular joint disorder.

f OAT: oral appliance therapy.

g ESS: Epworth Sleepiness Scale.

h FOSQ: Functional Outcomes of Sleep Questionnaire.

i PSQ-18: Patient Satisfaction Questionnaire.

j AHI: apnea–hypopnea index.

k RDI: respiratory disturbance index.

l HSAT: home sleep apnea test.

m MDA: mean disease alleviation.

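### Bruxism is listed as a secondary outcome but is measured only before or at appliance delivery, so post-treatment bruxism cannot be estimated

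*Protocol article*

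**What the plan says.** The Abstract (Methods) names bruxism among the outcomes: "Secondary outcomes include daytime sleepiness, sleep-related quality of life, patient satisfaction, oral appliance–related side effects, and bruxism". Table 1 has two bruxism rows. The patient row has the secondary-outcome role, the BruxScreen-Q as its instrument and Visit 1b as its only time point. The clinician row reads "Predictor and clinical assessment BruxScreen-C questionnaire and dental exam Visit 1 a", so it is not an outcome and is also collected once.

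The section on patient-completed measures confirms the timing of the patient form: "They will also undergo a bruxism screening assessment at baseline (visit 1b) using the BruxScreen-Q". The Table 1 footnotes define the two visits: "Visit 1a = eligibility screening, consent, and baseline dental examination/clinical assessment" and "Visit 1b = oral appliance delivery and baseline questionnaires".

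The Statistical Analysis Plan section says that primary and secondary outcomes will be summarised descriptively, for the whole cohort and by titration approach. It specifies no model or test for bruxism.

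**The concern.** An outcome has to be observed after the exposure has had a chance to act. Titration runs for about 8 weeks from appliance delivery, with follow-up at about 4 and 8 weeks. Both bruxism measurements fall before or at delivery. The role that the article gives to bruxism and the schedule that it sets for it therefore contradict each other.

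Followed as written, the plan would report bruxism by titration approach under the secondary outcomes. In a nonrandomized study the two groups may well differ in bruxism before treatment, through differences between practitioners or in patient selection. Such a difference would describe who was enrolled, but its place in the report would invite reading it as a result of titration.

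**Working it through.** No sample-size or power figure bears on this point, and the plan gives no figure to reproduce. The check is a count, from Table 1, of scheduled assessments after delivery (Visit 2 or Visit 3) for every row with a secondary-outcome role.

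| Secondary outcome in Table 1 | Time points | Assessments after delivery |
|---|---|---|
| Daytime sleepiness (ESS) | 1b, 2, 3 | 2 |
| Sleep-related quality of life (FOSQ-10) | 1b, 2, 3 | 2 |
| Patient-reported side effects | 1b, 2, 3 | 2 |
| Clinician-observed side effects | 2, 3 | 2 |
| Patient satisfaction (PSQ-18) | 3 | 1 |
| Bruxism (BruxScreen-Q) | 1b | 0 |

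Bruxism is the only one of the six rows with a count of zero. Adding the clinician form does not change this, because BruxScreen-C is collected at Visit 1a only.

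The next step was to look for bruxism data at follow-up elsewhere in the article.

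- **Side-effect items.** The patient items are jaw pain, tooth discomfort and bite changes. The clinician items are dental discomfort and occlusal changes. None names bruxism.
- **Study Schedule of Assessments.** The descriptions of Visits 2 and 3 mention titration, adherence data, questionnaires or patient-reported outcomes, and sleep testing. They do not mention bruxism.
- **Dentist-Completed Clinical Forms.** One sentence says that dentists complete forms from Visit 1a to Visit 3, and the list of form contents includes BruxScreen-C. But the list covers the whole form set, including eligibility and STOP-BANG, which Table 1 places at Visit 1a only. The sentence refers to Table 1 for the detail, and Table 1 places BruxScreen-C at Visit 1a only.

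The article thus schedules no bruxism measurement after delivery.

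**The case against.** **The label may be the only mistake.** Both instruments are scheduled before or at delivery, the clinician form is already a predictor, and the text calls the patient form a screening assessment. This pattern fits a baseline characteristic that was given the wrong role. The reading is plausible and the documents do not exclude it. It bears on which fix is right, but the contradiction remains until one of the two statements is changed.

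**The full protocol or a separate analysis plan may settle it.** This does not stand. An article may leave detail to other documents, but here it fixes both the role and the time point, and presents Table 1 as the full summary of variables, roles and timing. No analysis plan can supply values that are not collected.

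**The harm is limited.** This stands in part. No bruxism test is planned, and a reader who notes the visit label would not take a baseline table for a treatment effect. The primary outcome (mean disease alleviation), the feasibility measures and the other secondary outcomes are untouched.

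Two stronger readings are tempting, and the documents support neither. A reader might infer that a stated secondary objective cannot be met. The Abstract's objective speaks only of treatment effectiveness and patient-centered outcomes, the Introduction states only a primary objective, and neither mentions bruxism. A reader might also infer that bruxism cannot be analysed at all. The baseline values can be described and used as a covariate; what is lost is any estimate of bruxism after treatment.

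**Conclusion.** The point holds as a contradiction between role and schedule. Bruxism has no scheduled assessment after delivery, against one or two for each of the other five secondary-outcome rows. None of the 60 planned patients has a scheduled value from which change, or a difference between approaches after titration, could be estimated. The summary by approach would present a pre-treatment characteristic as an outcome.

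The conclusion assumes that Table 1 is complete, as the article presents it, and that the general sentence on dentist forms adds no visit beyond Table 1. The consequence is confined to one secondary outcome in a feasibility study. It should be corrected, but it does not threaten the primary analysis.

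**What to change.** Choose one of two changes, according to what was intended.

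1. **Keep bruxism as an outcome.** Add BruxScreen-Q to the electronic questionnaires already completed at Visit 3, and summarise the Visit 3 values by titration approach, accounting for the Visit 1b value. The cost is one more form at an existing visit and a minor amendment, which needs ethics board approval. Recruitment began in late 2025 and is projected through January 2027, so patients who have passed Visit 3 before the change will lack the value; the article does not say how many that would be. It also describes BruxScreen-Q only as a screening tool and does not show that it captures change over 8 weeks. The authors would need to justify that use first.

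2. **Treat bruxism as a baseline characteristic.** Reclassify the BruxScreen-Q row in Table 1 as a baseline predictor or covariate, and drop bruxism from the secondary outcomes in the Abstract and Table 1. This changes wording only and adds no data collection. The cost is that the study then makes no statement about bruxism after treatment.

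The second option follows from the documents as they stand. The first is worth its cost only if bruxism after treatment is of real interest, and the number of patients without a Visit 3 value grows with delay.

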#### Dentist-Completed Clinical Forms

Dentists will complete standardized electronic case report forms at screening (visit 1a), baseline (visit 1b), and follow-up visits (visits 2 and 3), as summarized in Table 1. These forms capture dentist and dental practice characteristics, eligibility confirmation, OSA risk screening (STOP-BANG) [31], bruxism screening using the BruxScreen-C [30], dental and airway characteristics, and oral appliance type.

#### Objective Physiologic and Adherence Measures

Physiologic sleep measures are obtained using the NightOwl HSAT device, with assessments conducted at baseline and follow-up visits as specified in Table 1. Objective adherence is measured using the DentiTrac compliance tracker embedded within the oral appliance, which records nightly usage duration and head position. Adherence data are collected continuously and summarized at follow-up visits.

#### Derived Outcomes and Data Integration

The primary outcome, MDA, is derived by integrating physiologic efficacy (change in AHI) with objective adherence, as described in Table 1. Secondary and exploratory outcomes include patient-reported measures, clinician-observed effects, and feasibility indicators. All data sources are linked to participant study identifiers within REDCap to support centralized data management and analysis.

#### Sample Size

Sixty patients will be enrolled across 10 dentist clusters (approximately 6 patients per dentist). This sample size was determined to support feasibility objectives and to estimate variability in the primary outcome (MDA) [7,10] while accounting for clustering of patients within dentists. Assuming a 2-sided α of .05 and 80% power, the study is capable of detecting standardized differences in MDA ranging from approximately 0.82 to 0.97, depending on assumptions regarding intracluster correlation coefficients (5%‐10%) and allocation ratios between titration approaches (4:6 or 3:7). These calculations account for an anticipated attrition rate of 10%‐20%.

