### Study Population

The study population comprises adult patients receiving OAT for OSA in participating dental practices within the STOHN. Eligible participants must meet the following criteria: (1) be aged 18 years or older; (2) have a confirmed diagnosis of OSA established by a qualified sleep physician; (3) have a referral for OAT with a scheduled oral appliance delivery visit at a participating site; (4) be able to communicate in English; (5) have access to email or text messaging for study communication; (6) be willing to complete HSAT using the NightOwl device [16,17]; (7) agree to use an oral appliance embedded with an objective compliance tracker (DentiTrac) [15].

Participants will be excluded if they: (1) lack a physician-confirmed diagnosis of OSA;

(2) have a history of OSA-related surgical treatment (eg, tonsillectomy and/or adenoidectomy or uvulopalatopharyngoplasty [UPPP]); (3) are unable to provide reliable contact information; and (4) decline participation in device-based monitoring. Participants are recruited consecutively from eligible patients receiving routine clinical care at participating sites. The titration approach is determined by the treating practitioner and applied consistently to enrolled patients within each practice.

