#### Statistical Analysis Plan

Descriptive statistics will be used to summarize dentist- and patient-level characteristics, as well as primary and secondary outcomes. Continuous variables will be reported as means and standard deviations or medians and interquartile ranges, and categorical variables will be summarized using frequencies and percentages. Results will be presented for the overall cohort and stratified by titration approach. The primary analysis will evaluate differences in mean MDA between standard and enhanced titration approaches using generalized estimating equation mixed-effects models to account for clustering of patients within dentists. The titration approach will be modeled as a dichotomous independent variable. The distribution of MDA will be assessed, and transformations will be applied if necessary to meet model assumptions.

Potential confounders at the dentist and patient level will be similarly assessed, specifically, whether they are associated with the outcome, change in MDA, and with the primary independent variable, titration approach (signs and symptoms or multimethod positioning). The primary suspected and potential confounders at the dentist level will be age, practice type, and setting, and specialty. At the patient level, demographics will be similarly assessed. Typically, suspected or potential confounders would be entered in the model, and if they retained a set level of statistical significance or changed the magnitude of association between titration method and change in MDA, they would be retained as confounders. However, in this feasibility study, it is likely that the model will not converge, especially for dentist characteristics. The inability to adjust for them will be a limitation of the study and a point of discussion. Baseline OSA severity will be adjusted as a continuous variable, and depending on the distribution, may be categorized as mild, moderate, or severe. Missing data are an aspect of feasibility that will be measured and reported as such, especially for the primary variables.

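### With one titration approach per dentist, 10 dentists leave about 8 degrees of freedom, so power at 0.82 to 0.97 SD is about 69%, not 80%; dentists using both approaches narrow the gap

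*Protocol article*

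**What the plan says.** The Sample Size section plans 60 patients under 10 dentists, about 6 each. It claims: "Assuming a 2-sided α of .05 and 80% power, the study is capable of detecting standardized differences in MDA ranging from approximately 0.82 to 0.97". The range is said to reflect an ICC of 5% to 10% and "allocation ratios between titration approaches (4:6 or 3:7"). The section adds that attrition of 10% to 20% is already allowed for. It names no formula, reference distribution or degrees of freedom.

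The Statistical Analysis Plan section compares mean MDA between approaches with "generalized estimating equation mixed-effects models to account for clustering of patients within dentists".

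The article gives two accounts of the level at which the approach is set:
- Study Population says: "The titration approach is determined by the treating practitioner and applied consistently to enrolled patients within each practice". Practitioner criterion 5, under Study Design and Setting, likewise asks for one defined approach for all of a dentist's enrolled patients.
- The opening of Study Design and Setting says that dentists who use both approaches apply their usual one to their first 3 patients and are asked to use the other for the rest. The limitations paragraph of the Discussion also relies on a within-practitioner approach. Yet Study Design and Setting further says that no switching is mandated.

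**The concern.** A design effect enlarges the variance of the treatment contrast. It does not allow for that variance having to be estimated from only 10 clusters. If each dentist uses one approach, the contrast lies wholly between dentists, and normal quantiles are too small for it. The printed pairing of 5% two-sided error with 80% power would then not be attainable at the printed differences.

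The article presents the range as what the study can detect, and the study is meant to inform later trials. A reader planning another trial with few dentists could reuse the same method and undersize it.

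**Working it through.** **Inputs (Sample Size section).** Two-sided α 0.05; power 80%; N = 60; 10 dentists; m = 6 patients per dentist; ICC 0.05 or 0.10; allocation 4:6 (24 v 36 patients) or 3:7 (18 v 42).

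**Step 1: reproduce the printed range.** In SD units:

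SE = √{[1 + (m − 1) × ICC] × (1/n₁ + 1/n₂)}, and detectable difference = (1.960 + 0.842) × SE.

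For 24 v 36 and ICC 0.05: SE = √(1.25 × 0.06944) = 0.2946, and 2.802 × 0.2946 = 0.825.
For 18 v 42 and ICC 0.10: SE = √(1.50 × 0.07937) = 0.3450, and 2.802 × 0.3450 = 0.967.

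These match the printed ends. A t reference on 58 df gives 0.839 to 0.983. The normal formula with 54 or 48 analysed (m = 5.4 or 4.8) gives 0.860 to 0.998 or 0.900 to 1.037. None of these fits as well, so the normal formula with all 60 patients is a strong inference, though only an inference.

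**Step 2: the degrees of freedom that this design effect implies.** The factor 1 + (m − 1) × ICC applies when all of a dentist's patients share one approach. A dentist mean then has variance ICC + (1 − ICC)/6, which is 0.2083 at ICC 0.05. Comparing 4 with 6 dentist means gives SE = √{0.2083 × (1/4 + 1/6)} = 0.2946, the same as in step 1. The variance is estimated from 10 means less two group means, so df = 8 and the critical value is 2.306 instead of 1.960.

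**Step 3: power and detectable difference with noncentral t on 8 df, N = 60.** The multiplier for 80% power is 3.20 × SE instead of 2.80 × SE.

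| Allocation | ICC | SE | Normal formula, 80% | Power there, 8 df | 80% detectable, 8 df |
|---|---|---|---|---|---|
| 4:6 | 0.05 | 0.2946 | 0.825 | 69.0% | 0.943 |
| 4:6 | 0.10 | 0.3227 | 0.904 | 69.0% | 1.033 |
| 3:7 | 0.05 | 0.3150 | 0.882 | 69.0% | 1.008 |
| 3:7 | 0.10 | 0.3450 | 0.967 | 69.0% | 1.104 |

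At the rounded ends, power is 68.5% at 0.82 (4:6, ICC 0.05) and 69.3% at 0.97 (3:7, ICC 0.10). Simulation of the dentist-mean t test at the four normal-formula differences (300,000 runs each) gave 69.0% to 69.2%.

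**Step 4: the stated attrition, one approach per dentist, 8 df.** With 54 analysed the 80% range is 0.98 to 1.14, and power is 65% at 0.82 and 67% at 0.97. With 48 analysed the range is 1.03 to 1.18, and power is 61% and 63%.

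**Step 5: keeping 1.96 does not restore the claim.** In the same layout, referring the statistic to 1.96 gives a true type I error of about 8.6% with a pooled dentist-level SE, and about 12.5% to 15.6% with an uncorrected sandwich-type SE.

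**Step 6: some dentists use both approaches.** The article does not say how many will, so the number is an assumption. Such dentists are taken to split 3/3, with 60 analysed, a generalized-least-squares variance and 8 df as an approximation.

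| Dentists using both | ICC 0.05, power at 0.82 | ICC 0.10, power at 0.90 |
|---|---|---|
| 0 | 68.5% | 68.6% |
| 2 | 71% | 74% |
| 4 | 74% | 79% |
| 6 | 76% | 83% |
| 10 | 81% | 89% |

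The rows for 0 to 6 keep 24 v 36 overall. The last row is necessarily 30 v 30, outside the stated ratios. Within-dentist contrasts also draw on patient-level residual information, so 8 df probably understates power in the rows with such dentists.

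**The case against.** The strongest reply is that the 69% belongs to only one of the two designs that the article describes. Where dentists contribute both approaches, part of the contrast is within dentist, its variance is smaller, and more than 8 df may apply. This stands. A reader might infer that every test holding 5% falls about 11 points short, or that the shortfall has nothing to do with dentists who use both approaches. The documents support neither reading: step 6 shows the gap closing as their number rises, and faster at ICC 0.10.

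A second reply is that the formula and the dentist-level allocation are inferred, since the ratios are given between approaches and not explicitly between dentists. This is fair. However, the match at both ends is close, and the design effect that produces it presupposes one approach per dentist.

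A third reply is that small-sample methods for GEE or mixed models are usually left to an analysis plan, which is not shown. That is right, and their absence from the article is not criticised here. The point concerns a printed figure. In the one-approach layout, a later small-sample correction would hold 5% but deliver about 69% power.

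A fourth reply is that this is a feasibility study whose main aims are recruitment, retention, data completeness, protocol adherence and preliminary effect sizes. This limits the weight of the point, since no stated decision depends on 80% power. It does not make the printed figure correct.

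**Conclusion.** The point holds conditionally. If each dentist uses one approach, as the reproduced design effect and the Study Population section both imply, the stated 80% power is about 69% at the printed differences. The range detectable with 80% power is then about 0.94 to 1.10 SD with all 60 analysed, some 0.12 to 0.14 SD above the printed range. This rests on the inferred formula, equal clusters of 6, and the article's own ICC and allocation values.

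If some dentists use both approaches, the shortfall is smaller: roughly 71% to 76% power for 2 to 6 such dentists at 4:6, ICC 0.05, a difference of 0.82 and 8 df. It may disappear with more such dentists, a higher ICC or more degrees of freedom. The feasibility aims are unaffected.

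**What to change.** First reconcile Study Design and Setting with Study Population on whether a dentist uses one approach or both, and on whether switching is requested. Until that is settled, no single range is right.

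Then recompute the Sample Size figure with a small-cluster t reference and the number of patients actually analysed. If the answer is one approach per dentist, state one of the following:
- about 0.94 to 1.10 SD at 80% power with all 60 analysed, and with the stated attrition about 0.98 to 1.14 SD (54 analysed, 10%) to 1.03 to 1.18 SD (48 analysed, 20%); or
- about 69% power at 0.82 to 0.97 SD, marked as before attrition.

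If some dentists use both, state the assumed number and the degrees of freedom used. In either case, make the attrition sentence agree with the figure. Printing 0.94 to 1.10 directly before a statement that losses are already counted would leave the section wrong.

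The cost is a recalculation and a few sentences of text. Enrolment need not change. The only drawback is a less favourable stated figure, which a feasibility study can accept.
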